## Abstract

**Background:**

Permanent supportive housing (PSH) is an evidence-based practice to address homelessness that is implemented using 2 distinct approaches. The first approach is place-based PSH (PB-PSH), or single-site housing placement, in which an entire building with on-site services is designated for people experiencing homelessness. The second approach is scatter-site PSH (SS-PSH), which uses apartments rented from a private landlord while providing mobile case management services.

**Objective:**

This paper describes the protocols for a mixed methods comparative effectiveness study of 2 distinct approaches to implementing PSH and the patient-centered quality of life, health care use, and health behaviors that reduce COVID-19 risk.

**Methods:**

People experiencing homelessness who are placed in either PB-PSH or SS-PSH completed 6 monthly surveys after move-in using smartphones provided by the study team. A subsample of participants completed 3 qualitative interviews at baseline, 3 months, and 6 months that included photo elicitation interviewing. Two stakeholder advisory groups, including one featuring people with lived experience of homelessness, helped guide study decisions and interpretations of findings.

**Results:**

Study recruitment was supposed to occur over 6 months starting in January 2021 but was extended due to delays in recruitment. These delays included COVID-19 delays (eg, recruitment sites shut down due to outbreaks and study team members testing positive) and delays that may have been indirectly related to the COVID-19 pandemic, including high staff turnover or recruitment sites having competing priorities. In end-July 2022, in total, 641 people experiencing homelessness had been referred from 26 partnering recruitment sites, and 563 people experiencing homelessness had enrolled in the study and completed a baseline demographic survey. Of the 563 participants in the study, 452 had recently moved into the housing when they enrolled, with 272 placed in PB-PSH and 180 placed in SS-PSH. Another 111 participants were approved but are still waiting for housing placement. To date, 49 participants have been lost to follow-up, and 12% of phones (70 of the initial 563 distributed) were reported lost by participants.

**Conclusions:**

Recruitment during the pandemic, while successful, was challenging given that in-person contact was not permitted at times either by program sites or the research institutions during COVID-19 surges and high community transmission, which particularly affected homelessness programs in Los Angeles County. To overcome recruitment challenges, flexible strategies were used, which included extending the recruitment period and the distribution of cell phones with paid data plans. Given current recruitment numbers and retention rates that are over 90%, the study will be able to address a gap in the literature by considering the comparative effectiveness of PB-PSH versus SS-PSH on patient-centered quality of life, health care use, and health behaviors that reduce COVID-19 risk, which can influence future public health approaches to homelessness and infectious diseases.

**Trial Registration:**

ClinicalTrials.gov NCT04769349; https://clinicaltrials.gov/ct2/show/NCT04769349

**International Registered Report Identifier (IRRID):**

DERR1-10.2196/46782

## Introduction

The COVID-19 pandemic has made housing and health care for people experiencing homelessness an important priority for the health care and public health systems in the United States. Due to this population’s preexisting vulnerabilities [1-3] and difficulties in maintaining social distance and hygiene, researchers predicted at the outset of the COVID-19 pandemic that, without intervention, people experiencing homelessness would experience a 2-4 times higher risk of COVID-19 complications and fatality than the general population [4]. As a result of these concerns, more than US $2 billion from the US federal government’s Coronavirus Aid, Relief, and Economic Security Act was aimed at protecting people experiencing homelessness by reducing shelter densities and placing people in more secure housing options.

Permanent supportive housing (PSH)—programs that provide immediate access to independent living situations coupled with support services—represent one of the most studied and effective approaches for serving highly vulnerable people experiencing homelessness [5]. Numerous studies have demonstrated PSH’s effectiveness in improving housing retention, quality of life, and HIV outcomes. Nevertheless, a 2018 report by the National Academy of Medicine of the National Academies of Sciences noted the need for more research on PSH to establish what would constitute “housing-sensitive [health] conditions”—conditions whose transmissibility, course, and medical management are particularly influenced by homelessness and housing placement [5]. Two years after this report, COVID-19 and rapid policy decisions to address homelessness and expand housing during the pandemic offered a rare opportunity to address this gap in knowledge and advance research on housing as a social determinant of health.

This paper describes the protocols for the Person-Centered Housing Options, Outcomes, Services, and Environment (PCHOOSE) study, which examined the comparative effectiveness of 2 distinct approaches to implementing PSH. The first approach is place-based PSH (PB-PSH), or single-site housing placement, in which an entire building with on-site services is designated for people experiencing homelessness. The second approach is scatter-site PSH (SS-PSH), which uses apartments rented from a private landlord while providing mobile case management services. The limited research related to the comparative effectiveness of PB-PSH versus SS-PSH has been mixed. A meta-analysis of 8 studies with more than 3000 participants found 84% of people experiencing homelessness with mental disorders preferred SS-PSH [6], despite greater feelings of social isolation than those in PB-PSH. This is supported by qualitative research that has found people experiencing homelessness dislike the rules and limited privacy of PB-PSH [6-8]. Other studies have suggested PB-PSH may provide more supportive services [9] and may be more effective than SS-PSH in improving disability severity, community integration, and recovery [10]. Individuals with substance use disorders, those living with HIV, veterans, and women may also benefit more from PB-PSH programs than other populations because of the strong sense of community and mutual support they offer [11]. The PCHOOSE study intended to add to this literature by considering the comparative effectiveness of PB-PSH versus SS-PSH on patient-centered quality of life, health care use, and health behaviors that reduce COVID-19 risk.

## Methods

### Setting and Conceptual Model

The PCHOOSE study is situated in Los Angeles County, California, which has the nation’s largest unsheltered homeless population [12]. Los Angeles County also represents the country’s largest natural experiment in housing interventions to protect people experiencing homelessness [13] due to a major taxpayer-funded US $1.2 billion homelessness initiative passed in 2016 that resulted in the opening of thousands of new PSH units in Los Angeles County during the pandemic [14]. The study followed a diverse sample of people experiencing homelessness placed in either PB-PSH or SS-PSH for 6 months; barriers and facilitators that may affect PSH implementation during the pandemic and its aftermath were also investigated. The study was guided by the Gelberg-Anderson behavioral model for vulnerable populations [15], which involves examining predisposing, enabling, and need factors that contribute to health behaviors and patient-centered outcomes (see Figure 1). PSH is positioned as a key enabling factor for people experiencing homelessness with the hypothesis that PSH type (ie, PB or SS) will affect THE quality of life (general life satisfaction; physical, mental, social, and environmental health, including housing and neighborhood characteristics) and health behaviors, including health care use (eg, receipt of health care, mental health care, and social supports) and COVID-19–related prevention practices. We also expected that changes to our primary outcomes would affect the predisposing, enabling, and need characteristics of the people experiencing homelessness population over time.

**Figure 1 figure1:**
[figure not shown]
Gelberg-Anderson behavioral model for vulnerable populations (modified for PSH and COVID-19). PB: place-based; PSH: permanent supportive housing; SS: scatter-site.

In describing the protocols of the PCHOOSE study, this paper also highlights the challenges of conducting research with this vulnerable population in the United States during the highly dynamic COVID-19 pandemic. This includes steps taken to protect the research team, people experiencing homelessness participants, and PSH staff members, as well as the need to change survey instruments to reflect an evolving understanding of the COVID-19 virus, public health mitigation policies, and personal protective practices.

### Design Overview

This study leveraged Los Angeles County’s ongoing efforts to provide PSH to people experiencing homelessness during the COVID-19 pandemic using a mixed methods, prospective longitudinal design. We recruited people moving into PSH and provided them with smartphones with paid data plans to stay connected with the study for a 6-month period. All study participants were recruited through organizations that provide housing, supportive services, or both. Although PB-PSH is clearly defined in the homelessness services system, SS-PSH could have been officially categorized as a PSH program or a rapid rehousing program. Although rapid rehousing programs are typically short-term housing programs with time-limited and tailored assistance programs, during the pandemic, Los Angeles County expanded the use of rapid rehousing programs coupled with supportive services to quickly provide access to housing. Thus, for this study, we considered anyone receiving rapid rehousing assistance to be SS-PSH if they also received support services, and examined whether those receiving rapid rehousing differ in terms of demographics, health status, or homelessness histories.

For the study’s quantitative arm, participants completed a baseline survey followed by 5 monthly follow-up surveys once in housing. For the qualitative arm, we recruited a purposive subsample of people experiencing homelessness from both PB-PSH and SS-PSH who participated in 3 semistructured interviews; the first was an in-depth interview when they initially moved into PSH, followed by 2 follow-up interviews conducted 3 and 6 months later. Focus groups with housing providers from the affiliated housing agencies were also conducted. Study protocols for each study component are described separately in more detail.

To ensure that the study addressed questions important to people experiencing homelessness, providers, and policy makers and that the data were correctly interpreted, we also established 2 stakeholder advisory boards (SABs). The first advisory board is a lived experience group (LEG), which consists of 11 individuals who have personally experienced homelessness. The LEG meets quarterly and uses its lived experience, knowledge of what is important to people experiencing homelessness, and perspectives on how people experiencing homelessness may respond to study questions to inform recruitment strategies, interpretation of study findings, and dissemination efforts. The study’s second advisory board is a SAB, which consists of 15 providers, administrators, policy makers, and researchers with expertise in homelessness and housing programs in Los Angeles County. Due to concerns about meeting in person during the pandemic, all LEG and SAB meetings have been conducted remotely via Zoom.

### Ethics Approval

This human subjects’ research has been performed in accordance with the Declaration of Helsinki and approved by the University of Southern California’s Institutional Review Board (UP-20-01081) with a reliance agreement in place with the University of California, Los Angeles. All human subject participants provided informed consent via electronic signature. As described in more detail below, participants could receive up to US $105 in gift cards for participating in the quantitative survey component of the study and US $150 in gift cards for participating in the qualitative component of the study.

### Recruitment of Study Participants

People experiencing homelessness were eligible to participate in the study if they were 18 years or older, had been approved for PSH, could be interviewed in English or Spanish, and were willing to provide informed consent. Enrollment included people experiencing homelessness who had been approved for PSH in Los Angeles County and had either been housed in the past 2 weeks or were expected to be placed in housing in 30 days. PSH placement is determined through a county-run coordinated entry system that identifies clients’ needs and matches them with available housing options. Because the system typically assigns individuals approved for PSH to specific nonprofit, community-based agencies that are ultimately charged with securing housing and supportive services, recruitment was conducted through 26 agencies. The study began recruitment in January 2021 amid a significant surge in the COVID-19 pandemic in Los Angeles County. Therefore, in-person recruitment was not a viable option and instead depended on the case managers at each program, who were already interacting with people experiencing homelessness as part of the housing placement process. The study team relied on these agencies to inform anyone approved for PSH (or rapid rehousing who would be receiving supportive services) about the study. Study staff members then coordinated a meeting with the eligible people experiencing homelessness interested in the study via phone or Zoom to complete the enrollment process. Although this process remained largely intact throughout the recruitment period, in-person recruitment occasionally occurred when COVID-19 rates were low and visitors were allowed at program sites.

Recruitment for the qualitative portion of the study involved 2 sources. The qualitative people experiencing homelessness sample was selected from those who enrolled in the quantitative portion of the study. A subsample of study participants (N=40; 20 from each PSH model type) was selected for interviews using maximum variation sampling [16] based on demographic and health characteristics (ie, Black or African American people, women, individuals with chronic disease, individuals with serious mental illness, individuals with substance use disorders or individuals aged 60 years or older), and they separately consented to participate in qualitative interviews. The provider sample (N=48; 24 from each PSH model type) was selected from housing providers who worked at agencies that were study recruitment sites. Sites were asked to identify staff members who would be willing to participate in a focus group; staff members were asked to provide verbal consent at the outset of the focus group.

### Enrollment and Quantitative Data Collection Procedures

To enroll, an agency staff member initiated the referral process for people experiencing homelessness by contacting the research recruitment team via phone, email, or text. A research recruitment team member then followed up to schedule an appointment with the potential participant to complete a screening to ensure eligibility, review the consent form, and answer any questions related to the study protocols. Case managers then distributed study phones that had been shipped to the recruitment site. Participants received a Samsung A01 Core smartphone with an unlimited data and calling plan, which allowed them to provide electronic informed consent and complete a self-administered questionnaire sent via text message. Participants were enrolled in the study once they provided informed consent by completing a web-based form that assessed study comprehension and documented their electronic signature.

Initially, participants completed a 20-minute survey upon enrollment in the study to capture basic demographic and historical information about their housing and health. Baseline outcome measures were then administered in a follow-up survey approximately 1 day later to help reduce the burden involved in completing a lengthy questionnaire at the time of enrollment. Participants received a US $15 electronic gift card incentive for completing the baseline outcome measure survey. Participants who enrolled in the study prior to moving into a housing unit were asked to complete a second baseline outcome measures survey once they moved in and received another US $15 electronic gift card incentive. After moving into PSH and completing the demographic and baseline surveys, participants received 5 monthly follow-up surveys and received a US $15 electronic gift card incentive for each completed survey. Participants could also complete surveys over the phone if they preferred to speak with a surveyor rather than self-administer the survey. Electronic gift cards were sent to an email address provided by the participant. The survey links were all sent via text message. The study team, in consultation with the LEG, opted to allow “prefer not to answer” as a response option for all historical and monthly survey questions to reduce any frustration among those who were not sure how to answer and minimize the possibility that some questions could be triggering given high rates of past trauma.

### Quantitative Measures

Patient-centered quality-of-life outcomes in this study were based on the World Health Organization’s definition of health as “a state of complete physical, mental, and social well-being and not merely the absence of disease or infirmity” [17]. Table 1 describes the study’s constructs and measures, with the exception of COVID-19–related outcomes, which are discussed in more detail subsequently.

**Table 1 table1:** Study constructs and measures.

Construct		Variables and instruments
**Patients experiencing homelessness** **population characteristics: covariates measured at baseline only** **[18]**		
	Predisposing	Demographics (ie, age, gender, marital status, and veteran status); health beliefs (ie, knowledge of disease and health services attitudes); social structure (ie, race and ethnicity, education, employment, religion, trauma, and homelessness history); systems involvement history (eg, foster care, criminal justice, and trauma); housing preference
	Enabling	Income, insurance, benefits, case management, food insecurity, and social support
	Need	Chronic physical disease, serious mental illness, and substance use disorder; baseline measures for physical and mental health status as noted in outcomes
**Patient-centered outcomes: quality of life including physical, mental, social, and environment health, and measured monthly**		
	Life satisfaction	NIH^a^ Toolbox Item Bank v2.0 General Life Satisfaction (10 items, self-rated life satisfaction) [19]
	Physical health	PROMIS^b^ Global Health Scale Version 1.2 (PROMIS; 2 items, self-rated physical health and activities) [19]
	Mental health	PROMIS (2 items, self-rated mental health, frequency bothered by symptoms) [19]
	Social health	PROMIS (1 item, self-rated satisfaction with social activities and relationships) [19]
	Environmental health	Housing retention and Housing Environment Scale (4 items, residential satisfaction; 12 items, neighborhood quality and safety) [20]
**Health behaviors: measured monthly**		
	Substance use	Collaborating Consortium of Cohorts Producing NIDA^c^ Opportunities survey (12 items) [21]
	Health care use	COVID-19– and non-COVID-19–related past-180-day use of physical, mental, substance use, social services, and PSH^d^ support; medication adherence; ambulatory and emergency department visits and hospitalizations; barriers to care

^a^NIH: National Institutes of Health.

^b^PROMIS: Patient-Reported Outcomes Measurement Information System.

^c^NIDA: National Institute on Drug Abuse.

^d^PSH: permanent supportive housing.

### COVID-19–Related Outcomes

Given that the study project period began in October 2020, with initial recruitment starting in January 2021, our initial survey questions focused on COVID-19–related protective health behaviors that were salient at the time—namely, social distancing and handwashing. As science and the pandemic evolved, questions about COVID-19 testing and vaccines were introduced as key protective health behaviors. For COVID-19 testing on the monthly surveys, we first asked whether participants had been tested in the past 30 days and, if so, the outcome of the test. For anyone who had not been tested in the past 30 days, we asked about barriers to testing (ie, “Did you want to get tested for coronavirus [COVID-19] in the past 30 days but were unable to?”). For those who replied affirmatively, possible reasons for not getting tested included: I didn’t know how to make an appointment to be tested; I didn’t know where to go; I don’t think that I can afford the cost of the test; I didn’t have time to get tested; I am unable to travel to a testing location; I am worried about bad things happening to me or my family if I get tested (including discrimination, government policies, or social stigma).

For vaccination status, questions evolved over time. When the study began and there was only 1 approved vaccine that was not readily available, participants were asked if they “have been offered the COVID-19 vaccine?” with branch logic based on whether they said they had received the vaccine or would receive it if offered. If participants responded “no” to having received the vaccine after being offered it or to a hypothetical offer, they were prompted about the reasons for not receiving the vaccine to better understand their hesitancy. Six months into data collection, when multiple approved vaccines were more readily available, the survey was revised to first ask if a participant had received the vaccine rather than if it had been offered. Questions about the type of vaccine (brand) and the number of doses received were also added to the monthly surveys. In June 2022, the survey was revised a final time to ask new questions about receipt of COVID-19 booster vaccines using the following three uniform questions: (1) “How many doses of the COVID-19 vaccine have you received (including booster shots)? Please indicate the brand of each dose you received and the month and date when you received it”; (2) “To the best of your knowledge, have you received all COVID-19 doses or boosters that you’re eligible for?”; and (3) “In the future, how likely are you to receive another dose or booster of the COVID-19 vaccine if it’s recommended?” Participants who had already completed the study and not been asked these questions were recontacted.

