### Quantitative Analysis

The statistical analysis will rely on bivariate and multivariate regression analysis to examine the relationship between PSH (SS-PSH vs PB-PSH) and quality of life and COVID-19–related health behaviors. For outcomes, we will use a pre-post design that treats Month 1 as the baseline and Month 6 as the endline and compares pre-post changes for SS-PSH and PB-PSH. For outcomes sensitive to monthly trajectory variation, we will use fixed-effects and random-effects models of monthly outcomes that test for interaction between the PSH model and months of exposure to each PSH type. These models will be informed by an analysis of baseline variation between SS-PSH and PB-PSH clients. We expect variations in the level of baseline morbidity. Thus, we will use both multivariate models that account for baseline differences and propensity score matching models that establish an area of common support for SS-PSH and PB-PSH comparisons. We will use calendar-month controls to account for historic changes in the ecology of health behavior, particularly in relation to rising and falling rates of COVID-19. We will also address the potential need for multilevel or mixed-effects models to account for potentially shared experiences by housing and service providers. Additional models will test for differences in housing outcomes by race, ethnicity, sex, and gender via interaction effects and stratified models. Further analysis will entail the use of a path modeling framework to understand the pathways leading from PSH types to outcomes of interest. Due to the decision to include “prefer not to answer” as an option for all questions, all analyses will account for the frequent use of this response option. In cases where “prefer not to answer” is a common or meaningful response option, such as regarding partisan political affiliation or experiences of trauma, we will include it as a response option. In cases where “prefer not to answer” appears to reflect a random nonresponse pattern, we will treat the value as missing, use multiple imputations to maintain sample size, and conduct robustness checks comparing the imputed and raw samples.

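### Vaccination cannot reverse, so the planned Month 1 to Month 6 change comparison can bias the PSH-type contrast if Month 1 coverage, enrolment timing or recontact differs between the groups

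*Protocol article*

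**What the plan says.** **Measurement** (COVID-19–Related Outcomes). "For vaccination status, questions evolved over time". The questionnaire began with whether a vaccine had been offered and reached receipt through branching. About six months into data collection, "the survey was revised to first ask if a participant had received the vaccine rather than if it had been offered", with brand and number of doses added. From June 2022 three uniform questions were used, one of which asks: "Please indicate the brand of each dose you received and the month and date when you received it". For people who had already left the study: "Participants who had already completed the study and not been asked these questions were recontacted".

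**Analysis** (Quantitative Analysis). For outcomes in general, "we will use a pre-post design that treats Month 1 as the baseline and Month 6 as the endline"; the analysis then "compares pre-post changes for SS-PSH and PB-PSH". No exception is made for vaccination. A second route is given without listing which outcomes take it: "For outcomes sensitive to monthly trajectory variation, we will use fixed-effects and random-effects models of monthly outcomes". On period effects: "We will use calendar-month controls to account for historic changes in the ecology of health behavior". Regression adjustment for baseline differences and propensity score matching are also planned. The baseline difference that the section anticipates is in morbidity. Table 1 lists demographic, social, enabling and health-need covariates, and vaccination is not among them.

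**Context** (Results and Limitations). Placement was not randomised, recruitment ran from January 2021 to July 2022, and 272 place-based and 180 scatter-site participants were housed at enrolment. Limitations concedes changing instruments, period effects and possible errors in the vaccine data.

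**The concern.** Vaccination moves in one direction only. In a change score, everyone already vaccinated at Month 1 contributes zero, whatever the housing does. If one group starts with higher coverage, it has less room to change and can look less effective even when uptake among the unvaccinated is the same in both groups.

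Recontact raises a separate question about time windows. For an early enrolee, the uniform dose questions were answered long after Month 6. For a late enrolee they fell inside the six months. Without a cut-off at each person's own Month 6, a dose count covers unequal periods.

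At stake is the comparison of housing models on one of the main COVID-19 behaviours, in a study whose 19 months of recruitment spanned a rapid change in vaccine availability.

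**Working it through.** The article gives no power calculation, vaccination rate or enrolment month by housing type, so there is no design figure to reproduce. The participant counts agree: 641 − 37 − 20 − 21 = 563; 272 + 180 = 452; 452 + 111 = 563. The group sizes below come from Results. Coverage, uptake and recontact shares are assumptions.

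**1. Ceiling effect with no true housing effect.** Let b be the share vaccinated at Month 1 and h the share of the unvaccinated who are vaccinated by Month 6, with h equal in both groups. The expected change is (1 − b) × h.

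Example with 60% place-based, 40% scatter-site and h = 50%:
- place-based: 0.40 × 0.50 = 0.20
- scatter-site: 0.60 × 0.50 = 0.30
- false difference: 10 points
- SE = √(0.20 × 0.80/272 + 0.30 × 0.70/180) = 0.042, so z = 0.10/0.042 ≈ 2.4

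Other inputs, with an unpooled two-proportion z-test at two-sided 5%:

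| Month 1 coverage, place-based vs scatter-site | h | False difference | Rejection rate |
|---|---|---|---|
| 40% vs 40% | 10–50% | 0 | 5% |
| 30% vs 40% | 10%, 30%, 50% | 1, 3, 5 points | 7%, 13%, 20% |
| 30% vs 50% | 10%, 30%, 50% | 2, 6, 10 points | 15%, 38%, 64% |

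**2. Do the planned controls remove it?**
- *Calendar month.* If both groups enrol evenly over time, calendar month is unrelated to housing type. Adjusting for it then leaves the expected differences in the table unchanged.
- *Monthly person fixed-effects model.* The housing-by-month interaction still compares within-person change, and people vaccinated at Month 1 still contribute none.
- *Adjustment for Month 1 vaccination.* With equal h, E[Month 6 status | Month 1 status] = h + (1 − h) × Month 1 status. There is no housing term, so the expected effect is 0. This removes the bias, but only if that variable is in the model.

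**3. Recontact.** A person with Month 1 in January 2021 reaches Month 6 in June 2021 (January + 5 months). June 2022 is 12 months later. Suppose a share r of a group had the recontact answer used as its Month 6 value, with b = 40%, h = 30%, and a share e of those still unvaccinated vaccinated after exit. The added change is r × 0.60 × 0.70 × e = r × 0.42 × e.
- r equal in both groups: difference 0
- r = 70% vs 50%, e = 20–40%: 0.20 × 0.084 to 0.20 × 0.168 = 1.7 to 3.4 points
- r = 80% vs 40%, e = 20–40%: 0.40 × 0.084 to 0.40 × 0.168 = 3.4 to 6.7 points

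**4. Wording change (secondary).** If the early branching captured 80–90% of the vaccinated (b = 40%), each person whose Month 1 and Month 6 straddle the revision adds 0.40 × 0.20 = 8 or 0.40 × 0.10 = 4 points of false uptake on average. The group difference is 0 with equal straddling. It is 0.8 to 3.2 points at 40% vs 20% or 50% vs 10% straddling.

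**The case against.** A reader might infer several stronger claims that the documents do not support.

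- *That the analysis will produce a false housing effect.* The one-way state alone does not: with equal coverage, timing and recontact, every difference above is 0. The article reports none of these by housing type.
- *That recontact answers become the Month 6 value.* Nothing says so. Recontact gave earlier completers the same uniform questions with dose dates, and that is what makes the repair possible.
- *That the early questionnaire recorded offers rather than receipt.* Its branching already reached receipt. The revision changed which question came first and added detail.
- *That dose dates will go unused.* This would be an inference from silence in a condensed article. A full analysis plan may define the variable.

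Other objections also have force. Baseline adjustment is planned and would remove the example bias if it included Month 1 vaccination. Vaccination might be sent to the monthly models. The magnitudes rest on assumed rates, full group sizes, and no clustering or nonresponse. Limitations acknowledges the instrument and period problems.

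These objections limit the claim to a conditional one but do not remove it. The change rule is stated for outcomes with no exception, and the monthly alternative shares the ceiling. Vaccination is not named as a baseline covariate. Limitations promises later examination and sets no rule.

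**Conclusion.** The point holds conditionally. A Month 1 to Month 6 change comparison is poorly suited to a state that cannot reverse. It can bias the housing contrast if Month 1 coverage, enrolment timing or recontact differs by housing type. Such differences are plausible without randomisation and over 19 months of recruitment, but they are not shown.

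Direction and size cannot be determined from the documents. Under the assumed inputs, the ceiling effect ranges from 0 with equal coverage, through 1 to 5 points for a 10-point imbalance, to 10 points for 60% vs 40% coverage with 50% uptake. These figures take no housing effect to mean equal uptake among those not yet vaccinated. Calendar-month controls do not correct unequal Month 1 coverage. Adjusting for Month 1 vaccination would, and the article does not name it.

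**What to change.** State a rule for vaccination apart from the general change comparison:

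1. Derive status at Month 1 and at Month 6 from the dose dates in the June 2022 questions. Use the monthly answers given at the time where dates are missing.
2. Exclude every dose after the person's own Month 6, including doses learned of at recontact.
3. Analyse new vaccination by Month 6 among those not vaccinated, or not up to date, at Month 1, with calendar-month adjustment. At the least, adjust for Month 1 vaccination status in the full sample.
4. Report Month 1 coverage, enrolment month and recontact by housing type, so that readers can see whether the conditions for bias were present.

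With equal uptake among the unvaccinated, the at-risk analysis has an expected difference of 0 in every scenario above. This assumes accurate recalled dates and recontact response unrelated to housing type.

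The work is data derivation from items already collected. The costs are a smaller analysis set and reliance on recalled dates. The printed question asks for month and date, so check that the year was recorded. People still unvaccinated at Month 1 may differ between the groups in other ways, so the planned covariate adjustment remains necessary.
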